
### Work package 2: Air quality

We plan explore mechanisms of impact of the B-CAP on air quality using routinely collected air quality monitoring data, supplemented by citizen science collected air quality data around schools. We are able to add significant added value to our analyses by leveraging the extensive routine monitoring data, analysis protocols and outputs which are being undertaken as part of a national evaluation funded by DEFRA [39]. This will examine the 28 local authority areas (including Bradford) who are developing air quality plans and associated control sites. Using routinely collected air quality and traffic data the analysis will explore the impact of the clean air plans on pollution over and above underlying trends in air quality, traffic demand, transport use and the evolution of the vehicle fleet. Key outcomes will assess whether the B-CAP impacts on air quality. They will include routinely monitored air pollution (assessed via DEFRA national evaluation at 1 year and 3 years follow up) and mobile-sensed personal exposure to air pollution (assessed up to 6 months follow up).

#### Sampling and data collection methods

##### Routine air quality data

Council led routinely-collected hourly data of NO_2_ from seven continuous real-time monitoring stations (five of which are within the zone) will be extracted over the study period, supplemented by 400 NO_2_ Palmes diffusion tubes. Three of the continuous monitoring stations also measure PM_10_ and PM_2.5._ Data will be collated for 3 years prior, and 3 years post implementation.

##### Citizen science monitoring

Children are particularly vulnerable to the harmful effects of pollution, [53] and much of their exposure is experienced on their daily commute to and from school [54]. Children can be powerful agents for change, and as part of our planned evaluation we were keen to harness the enthusiasm of communities and young people by including them as ‘citizen scientists’ who could contribute to our research activities. Together with our public contributors we developed an air quality monitoring protocol which would involve primary school age pupils (aged 9-11) carrying mobile sensors on their journey to and from school. The aim is that these activities can be used to educate and inspire young people in issues regarding air quality and research.

We plan to recruit 12 schools to take part in citizen science air quality measurements which will involve installation of static sensors and diffusion tubes in key school locations recording PM and NO_2_, and ‘intensive observation periods’ where mobile sensors are carried by children during their school week and commute to school. Four schools will be located within the CAZ boundary, 4 schools will be located just outside the CAZ boundary (to explore any potential ‘displacement’ of pollution caused by drivers taking alternative routes to avoid the CAZ), and 4 schools will be distal (> 2 km) from the CAZ boundary.

We had planned that monitoring take place over a 24-month period (encompassing the year prior, and the year post CAZ implementation), however, lockdowns and school closures associated with the pandemic has meant this monitoring period has been reduced. For the intensive observation period we are now planning to measure children’s exposure at two time points pre-implementation (Autumn 2021, Spring 2022) and two time points post implementation (Summer 2022, Autumn 2022).

Within each school we will recruit 20 citizen scientists (total of *N* = 240) to measure pollution on their commute to and from school during parallel data collection periods across the 12 schools. Each pupil will carry the sensor for up to 5 days during each observation period, with data collected over 4 week observational periods within each school (a total of 20 days per pupil over 12 months). Atmotube Pro sensors (https://atmotube.com/products/atmotube-pro) which measure PM, volatile organic compounds (VOC), temperature and humidity, will be linked to a research smartphone which will also collect GPS tracks for their walk to and from school; these devices will be carried in a small waist/belt-bag. Children will be encouraged to engage in normal activity throughout the week. They will complete a short diary to record how they travelled to school, and locations visited each day. Detailed instructions and training will be given to pupils and parents.

Static sensors have been developed which use a Raspberry Pi Zero connected to two PM sensors: a Sensiron SPS30 PM sensor (which measures PM1, PM2.5 and PM10) and an Alphasense R2 optical particle counter which also gives more detailed particulate matter size information. Ambient temperature and relative humidity are also measured. Atmospheric data is logged every 10 seconds. Each school has the option to receive 3 static sensors; one outdoor and two indoor (one in a classroom and the other in a central location normally the dinner hall. All schools also have the option to receive a commercially available Purpleair PM2.5 sensors which displays data on a simple user friendly interface (https://map.purpleair.com/1/mPM25/a10/p2592000/cC0#10.89/53.7837/-1.7868) which is an effective tool for teaching and engagement. Triplicate NO_2_ tubes, which are changed monthly are installed at key outdoor locations for each school. A web dashboard to allow easy visualisation of pollution data collected via static and mobile sensors will be developed.

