### Aims and objectives

We aim to assess the impact of the B-CAP on attitudinal, behavioural, air pollution and health outcomes, and establish its cost-effectiveness, using a multi-outcome, multi-sector approach. We also aim to explore the factors influencing any impact (or lack thereof) and explore unintended or unanticipated outcomes. The impact of the B-CAP on health inequalities amongst different socio-economic and ethnic groups will be assessed across all outcomes. Our findings will enable the modelling of potential health impacts of a CAZ approach within other cities in the UK and internationally.

Our research questions are as follows:What are the key barriers and enablers to implementation of the B-CAP (including acceptability), and are there unintended consequences of the B-CAP for different stakeholder groups (e.g., increased health and economic inequalities)?Does the B-CAP affect travel choice behaviour and attitudes amongst people who live or work in Bradford at 12 months post implementation?Does the B-CAP reduce exposure to pollution amongst primary school age children up to 12 months post implementation?What is the impact of the B-CAP 3 years post-implementation on:respiratory health (primary outcome, as assessed by weekly counts of respiratory disease related emergency hospital or General Practice [GP] attendance) of children (aged < 18), adults (aged 18-64) and older adults (aged 65+)cardiovascular health (as assessed by weekly counts of cardiovascular disease related emergency hospital/GP attendance) of adults and older adults;birth outcomes such as low birth weight and preterm birth (assessed by monthly counts)How does the B-CAP impact on health inequalities up to 3 years post implementation?What is the value for money of the B-CAP 3 years post-implementation and longer term?

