What: Procedures	The Clean Air Zone is planned to go live in 2022. Daily charges for non-compliant vehicles will be £7 for taxis, £9 for light good vehicles and £50 for heavy goods vehicles. Prior to the go-live date, local businesses and taxi are able to access grants to contribute to the cost of upgrading or replacing their vehicles to CAZ standards with 25% of all grants prioritised for electric vehicles. Exemptions will be provided for local small/medium enterprises (SMEs), schools and charities. The CAZ to be supported by a range of other initiatives including: electric bus routes in key parts of the city with road space allocation to prioritise buses and reduce journey times; installation of alternative energy centres providing cost effective green refuelling/recharging facilities; travel planning with businesses to promote car sharing, active travel and public transport use amongst employees.
Who provides	The intervention is implemented by the Clean Air Plan delivery team within Bradford council. This includes an operations team, grants and business support, monitoring and evaluation, and ultra low emission vehicle programme.
How	Drivers can choose to pay the daily charge up to 7 days before and 7 days after entry. ANPR cameras at CAZ entry points will identify non-compliant vehicles by linking up with the Driver and Vehicle Licensing Agency database. Penalty charge notices will be sent to owners who do not pay within 7 days. Grants and exemptions will be applied for via the Breathe Better Bradford website.
Where	The Clean Air Zone boundary encompassing the city’s inner ring road, and a key corridor out to the North West of the city. It encompasses an area of 22.4 km2, primarily the most deprived inner city wards but including less deprived wards on the outskirts of the city. The boundary contains ~ 20% of the Bradford population.
When and how much	The Clean Air Zone is planned to be live until legal levels of pollution are reached
Tailoring	Clean Air Zone interventions are complex and tailored within each city that they are implemented within.
How well	A number of measures will be used to explore whether the B-CAP is implemented as intended. These will include: fleet composition; number of penalty notices issued; number of vehicles upgraded; number of grants applied for

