#### Analysis methods

Routinely collected air quality data will be analysed by the DEFRA national evaluation team in parallel to the current evaluation and will allow an analysis of trends in air quality across the district. The approach estimates the time-varying background levels of air quality from the Automatic Urban and Rural Network (AURN) of continuous monitoring stations for any given time point, and subtracts these from locally measured air quality data at roadside locations so that the contribution and trends associated with local traffic and the implementation of the B-CAP can be identified. As air pollution levels vary with fluctuations in emissions and dispersing air-flows, the underlying changes can only be established by ‘de-weathering’ and ‘de-seasoning’ local data [55]. Any abrupt or gradual changes in these trends around the intervention date of the B-CAP will then be estimated using change point detection methods [56].

The DEFRA evaluation methods for processing data will be adapted to deal with the additional data collected across our 12 schools within our intensive observation period (mobile sensing with *n* = 240 citizen scientists) and extended observation periods (continuous monitoring from static sensors).

The personal exposure of school citizen scientists (*n* = 240) before and after the introduction of the B-CAP will be mapped onto a 500 m × 500 m grid centred on each school. Any difference in levels, over the under-lying trends (as determined by the DEFRA evaluation project), will be attributed as impacts of the B-CAP. If the intervention is successful, it is expected that any differences would be greatest for the schools located within the CAZ boundary; however, as the CAZ may influence overall traffic volume and traffic flow, the benefits may extend beyond the CAZ boundary. Our study design allows us to explore any dose-response relationships with schools located on CAZ boundaries and distal to the CAZ boundary. We will explore differences using a 2 (pre/post) × 3 (location: inside, bordering or distal to CAZ) design using the Friedman test. Data from personal sensors will also be used to create an ‘exposure index’ along key transit routes to and from schools, allowing us to explore impact of the B-CAP on exposure during the school commute.

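### The mobile personal-exposure windows are not season-matched: spring falls only before go-live and summer only after, and the named pre/post test has no season term

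*Protocol article*

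**What the plan says.** Citizen science monitoring (Work package 2) fixes the intensive observation periods as "two time points pre-implementation (Autumn 2021, Spring 2022) and two time points post implementation (Summer 2022, Autumn 2022"). It explains that the schedule was first meant to cover the year before and the year after implementation, but "lockdowns and school closures associated with the pandemic has meant this monitoring period has been reduced".

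The participants are "primary school age pupils (aged 9-11) carrying mobile sensors on their journey to and from school". On numbers: "Within each school we will recruit 20 citizen scientists (total of *N* = 240"). Each pupil carries a sensor for up to 5 days per period, 20 days in all over 12 months, with data collected in parallel across the 12 schools: 4 inside the zone, 4 just outside and 4 distal.

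Under Analysis methods in Work package 2, the DEFRA processing methods are to be adapted to the school data, and a 2 (pre/post) by 3 (location) design is to be examined with the Friedman test. Any difference in levels over the underlying trends "will be attributed as impacts of the B-CAP". The same section says that underlying changes can be established only after weather and season have been taken out.

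On timing, Table 2 says "The Clean Air Zone is planned to go live in 2022" and names no month. Research question 3 asks "Does the B-CAP reduce exposure to pollution amongst primary school age children up to 12 months post implementation"; the opening of Work package 2 instead describes "mobile-sensed personal exposure to air pollution (assessed up to 6 months follow up").

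**The concern.** Season and period are partly confounded. One of the two windows on each side has no seasonal counterpart on the other, so an ordinary spring-to-summer change in particulate levels, or in how children travel, enters the pre/post comparison. The original 24-month schedule could have matched seasons. The shortened one cannot, except in autumn, and the article does not comment on the loss.

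What is at stake is a seasonal difference being read as an effect of the Bradford Clean Air Plan (B-CAP), or hiding one. The attribution sentence makes this easier, because it credits any difference over trend to the plan and not only the part by which inside schools differ from distal ones.

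Two secondary points follow from the same schedule. The windows are tied to calendar seasons while go-live is known only by year, and the follow-up horizon is stated in two ways.

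**Working it through.** **Stated figures.** 12 schools × 20 pupils = 240, and 4 windows × 5 days = 20 days per pupil. Both reproduce. Each zone has 4 × 20 = 80 pupils.

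**Layout.**

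| Season | Pre | Post |
|---|---|---|
| Autumn | 2021 | 2022 |
| Spring | 2022 | none |
| Summer | none | 2022 |

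**Bias of the pooled contrast.** Let A, Sp and Su be mean exposure in autumn, spring and summer with no CAZ effect, additive and stable between years.

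- Pre mean = (A + Sp)/2; post mean = (A + Su)/2.
- Post − pre = (Su − Sp)/2.
- Autumn pair alone: A − A = 0.

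The article gives no seasonal figures. If summer differs from spring by 10%, 20% or 30% in either direction (assumed), the spurious change is 5%, 10% or 15% of the spring level.

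**Effect on the test.** With two conditions the Friedman test is equivalent to the sign test. Take a two-sided 5% level (assumed; none is given for this component), independent pupils, and a seasonal shift of s standard deviations of the paired difference (assumed), so that a pupil's difference is positive with probability Φ(s).

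| s | Rejection rate, 240 pupils | Rejection rate, 80 pupils (one zone) |
|---|---|---|
| 0 | 4.5% | 3.3% |
| 0.1 | 22% | 8% |
| 0.2 | 68% | 24% |
| 0.3 | 96% | 50% |

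These rates ignore clustering within schools and any prior adjustment for season, so they illustrate the unadjusted test only.

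**What the zone contrast removes.** If season is additive and common to all zones, each zone carries the same (Su − Sp)/2 and inside minus distal is 0. If season is multiplicative, with summer differing from spring by a proportion d and inside levels r times distal, the remainder is (r − 1) × d/2 of the distal spring level. With d = 20% (assumed):

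- r = 1.25: 0.25 × 0.20/2 = 2.5%.
- r = 1.5: 0.50 × 0.20/2 = 5%.

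**Window labels.** As planned there are 2 pre and 2 post windows. If go-live falls after the summer window this becomes 3 and 1; if after the autumn window, 4 and 0. The article gives no rule for relabelling or moving a window.

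**Horizon.** Spring 2022 is labelled pre and the last window is Autumn 2022, so the last mobile measurement comes less than 12 months after go-live. That fits the 6-month statement in Work package 2, not a 12-month mobile result.

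**Pupil age.** Twenty days per pupil implies the same children in all four windows. If 9-11 is the age at recruitment in Autumn 2021, the range a year later is 10-12 and any final-year pupils have left primary school. If 9-11 describes one cohort aged 9-10 rising to 10-11, nobody leaves. The text does not settle which.

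**The case against.** The strongest reply is that season is already addressed. Background levels come from the national continuous monitoring network, and underlying trends from the DEFRA evaluation. A reader might infer that de-seasoning is impossible because it would have to be estimated from four short windows. The article does not support that: the adjustment comes from continuous data that cover every season on both sides. The distal schools are also measured at the same times, so a common additive season effect cancels in an inside-minus-distal contrast. Travel diaries and GPS tracks give some hold on changes in travel.

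Most of this stands, but it does not close the gap, for three reasons.

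- De-seasoning built for fixed roadside monitors does not capture seasonal change in how, when and where children travel, which is part of personal exposure. The mobile sensors record particulates and volatile organic compounds. Among the council's routine continuous stations, the article lists particulates at three and volatile organic compounds at none.
- A non-additive season effect survives the zone contrast.
- The attribution sentence is not limited to the zone contrast.

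A reader might also infer that many pupils, perhaps half, leave primary school before the autumn comparison. No year group is given and a single cohort fits the stated ages, so no number of leavers can be stated.

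Nor does the 12-month research question flatly contradict the 6-month statement. It says up to 12 months, and static school sensors are a separate, longer component. Finally, go-live slipping past a window is a contingency, not an error in the present text.

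**Conclusion.** The point holds in a limited form. The mobile windows are not season-matched, and the named test has no season term. Without adjustment, the pooled contrast carries (Su − Sp)/2, which is 5% to 15% of the spring level under the assumed 10% to 30% seasonal difference. The planned adjustment and the distal schools reduce this. In an inside-minus-distal contrast the remainder is zero if season is additive, and 2.5% to 5% of the distal level under the multiplicative figures assumed above. How well the DEFRA processing carries over to personal exposure cannot be judged from the article.

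The dependence of the labels on an undated go-live and the 6- versus 12-month wording are real but secondary. Pupil ageing is only a point to check. Severity is moderate: this is supplementary work on mechanism, and the primary respiratory analysis in Work package 3A does not use these windows.

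**What to change.** - Make Autumn 2021 against the first autumn after go-live the main mobile-exposure comparison, as a period-by-zone contrast against the distal schools, and report spring and summer as supportive. Alternatively, model all four windows with season terms and a period-by-zone interaction.
- Limit the attribution sentence to that contrast.
- Class each window as pre or post by the actual go-live date.
- Restate the mobile-exposure horizon in research question 3 as up to 6 months, to match Work package 2, and say which component, if any, covers 12 months.
- State the school year at recruitment. If any recruits were in their final primary year in Autumn 2021, the same-child autumn pairs shrink, and a school-level repeated cross-section analysis could be used.

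The cost is mainly wording and analysis. No new data are needed unless go-live falls after the Autumn 2022 window. The main contrast would use two of the four windows, 10 of the 20 days per pupil, so precision is somewhat lower.

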#### Analysis methods

Routinely collected air quality data will be analysed by the DEFRA national evaluation team in parallel to the current evaluation and will allow an analysis of trends in air quality across the district. The approach estimates the time-varying background levels of air quality from the Automatic Urban and Rural Network (AURN) of continuous monitoring stations for any given time point, and subtracts these from locally measured air quality data at roadside locations so that the contribution and trends associated with local traffic and the implementation of the B-CAP can be identified. As air pollution levels vary with fluctuations in emissions and dispersing air-flows, the underlying changes can only be established by ‘de-weathering’ and ‘de-seasoning’ local data [55]. Any abrupt or gradual changes in these trends around the intervention date of the B-CAP will then be estimated using change point detection methods [56].

The DEFRA evaluation methods for processing data will be adapted to deal with the additional data collected across our 12 schools within our intensive observation period (mobile sensing with *n* = 240 citizen scientists) and extended observation periods (continuous monitoring from static sensors).

The personal exposure of school citizen scientists (*n* = 240) before and after the introduction of the B-CAP will be mapped onto a 500 m × 500 m grid centred on each school. Any difference in levels, over the under-lying trends (as determined by the DEFRA evaluation project), will be attributed as impacts of the B-CAP. If the intervention is successful, it is expected that any differences would be greatest for the schools located within the CAZ boundary; however, as the CAZ may influence overall traffic volume and traffic flow, the benefits may extend beyond the CAZ boundary. Our study design allows us to explore any dose-response relationships with schools located on CAZ boundaries and distal to the CAZ boundary. We will explore differences using a 2 (pre/post) × 3 (location: inside, bordering or distal to CAZ) design using the Friedman test. Data from personal sensors will also be used to create an ‘exposure index’ along key transit routes to and from schools, allowing us to explore impact of the B-CAP on exposure during the school commute.

For the extended observational period (static monitoring) we will generate an understanding of pollutant distribution in the area, we will use data interpolation between the sites alongside the annual pollutant profiles close to the project schools.

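### The Friedman test named for the 2 × 3 school exposure design cannot test whether the pre/post change differs by location

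*Protocol article*

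**What the plan says.** Under Work package 2, Analysis methods, the protocol article fixes both the layout and the test for the children's exposure data: "We will explore differences using a 2 (pre/post) × 3 (location: inside, bordering or distal to CAZ) design using the Friedman test".

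The layout is set out under Citizen science monitoring:

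- Clusters: "We plan to recruit 12 schools to take part in citizen science air quality measurements".
- Location: "Four schools will be located within the CAZ boundary, 4 schools will be located just outside the CAZ boundary", and "4 schools will be distal (> 2 km) from the CAZ boundary".
- Pupils: "Within each school we will recruit 20 citizen scientists", 240 in total.
- Occasions: two before and two after the zone goes live.

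The question is also stated. The Abstract asks whether falls in pollution depend on closeness to the zone. Analysis methods expects the largest change at schools inside it and speaks of a dose-response across the location groups. The bordering schools are there to detect traffic displaced by drivers who avoid the zone. For this comparison the article names no other test, no interaction term and no unit of analysis.

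**The concern.** The question is whether the pre-to-post change differs between three groups of schools. That is an interaction between a within-unit factor (period) and a between-school factor (location). The Friedman test handles a single within-block factor, so the named method and the named design do not fit together.

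Two wrong readings could follow. If exposure falls inside the zone and rises at its border, which is the displacement the bordering schools were chosen to reveal, the opposite changes can cancel and the test reports nothing. If exposure moves equally at all 12 schools, the test can report a clear result that carries no evidence of a gradient. The second matters because Analysis methods attributes any difference beyond the underlying trend to the plan.

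**Working it through.** **1. The article's own figures.** 12 schools × 20 pupils = 240; 4 + 4 + 4 = 12 schools. Both agree with the text. No power calculation is given for this comparison, so there is none to reproduce.

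**2. What Friedman becomes with two levels.** With b blocks and k conditions, Q = 12/[b k(k+1)] × ΣR² − 3b(k+1), where R are the rank sums. For k = 2, let s be the number of blocks in which the first condition has the higher value. The rank sums are b + s and 2b − s, and Q reduces to (b − 2s)²/b. This is the sign test. Only the total count of rises and falls enters; location does not appear.

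**3. Location does not enter with four occasions either.** On a simulated 240 × 4 table the Friedman statistic was 2.93. It stayed at 2.93 after arbitrary constants were added by location, and again after the pupil rows were shuffled across locations.

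**4. Simulation of the planned layout.** There were 12 schools, 20 pupils each and four occasions, with pupils as blocks and α = 0.05 two-sided (assumed; none is stated). The intraclass correlation (ICC) is the school-by-period share of the variance around a pupil's own level. The article gives no value, so 0 to 0.20 was assumed. Effects are in standard deviations of that same variation. The comparator is one pre-to-post change per school, compared across three groups by an F test on 3 − 1 = 2 and 12 − 3 = 9 df.

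Proportion of runs rejecting, 1,000 runs per row:

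| Assumed truth | ICC | Friedman, 4 occasions | Sign test, pre/post | School-level F test |
|---|---|---|---|---|
| Inside −0.5, bordering +0.5, distal 0 | 0 | 0.055 | 0.032 | 0.998 |
| Same | 0.05 | 0.211 | 0.095 | 0.936 |
| −0.5 at all schools, no gradient | 0 | 1.000 | 1.000 | 0.045 |
| Same | 0.05 | 1.000 | 1.000 | 0.045 |

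The 0.211 and 0.095 at ICC 0.05 are not power. They are no higher than the rejection rates with no effect at all, shown next.

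**5. Type I error if pupils are the blocks.** There was no true effect, and 2,000 runs per row. Design effect = 1 + (20 − 1) × ICC; effective N = 240 / design effect.

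| ICC | Design effect | Effective N | Friedman, 4 occasions | Sign test, pre/post | School-level F test |
|---|---|---|---|---|---|
| 0 | 1.00 | 240 | 0.049 | 0.048 | 0.044 |
| 0.01 | 1.19 | 202 | 0.077 | 0.060 | 0.040 |
| 0.05 | 1.95 | 123 | 0.224 | 0.118 | 0.050 |
| 0.10 | 2.90 | 83 | 0.375 | 0.185 | 0.052 |
| 0.20 | 4.80 | 50 | 0.570 | 0.288 | 0.055 |

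**6. A fix that would not work.** Testing the interaction on pupil-level change scores gave type I error of 0.193, 0.336 and 0.540 at ICC 0.05, 0.10 and 0.20. A mixed model with random intercepts for school and pupil only has the same weakness, because it judges the interaction against pupil-level residual variation. A small check at ICC 0.10 rejected in about 40% of 100 runs.

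**The case against.** **The analysis is exploratory.** This stands and limits the severity. The primary outcome is respiratory attendances, analysed by segmented regression, and nothing there depends on this test. In addition, the third research question asks only whether exposure falls, and a test of overall change speaks to that. But the article also names a location factor and a proximity question, and the test cannot address either.

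**Details belong in an analysis plan.** The article names the test and the design together, so this is a method wrongly fixed, not one left open.

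**Friedman could be applied differently.** Running it separately within each location group yields three tests of change, and comparing their p-values does not test a difference in change. Using calendar days as blocks across schools monitored in parallel would compare locations within one period, but still not the change between periods.

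**The adapted national-evaluation methods deal with confounding.** They adjust for background, weather and season. They supply no test between location groups.

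**Clustering.** A reader might infer that the plan certainly ignores it. The article does not state the unit of analysis. Its repeated reference to 240 pupils suggests pupils as blocks, but averaging to 12 schools first would remove this problem and leave the structural one. Nor does a conventional school ICC translate into understated standard errors for location contrasts. Friedman produces no such contrasts, and stable school differences cancel in a pre-to-post change.

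**NO2.** Because the mobile sensors are ones "which measure PM, volatile organic compounds (VOC), temperature and humidity", and for static monitoring "we will use data interpolation between the sites alongside the annual pollutant profiles close to the project schools", a reader might infer that NO2, the pollutant targeted, goes untested. The documents do not support that. Seven continuous monitors and 400 diffusion tubes cover three years either side of implementation, with de-weathering and change-point detection for the routine data. Which pollutant should lead is a matter of preference.

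**Conclusion.** The point holds as a structural fault. The named test has no place for a between-school factor and no interaction, so it cannot answer whether change depends on proximity to the zone. That conclusion needs no assumed figure. The simulated sizes (3.2% to 5.5% detection of opposite changes against 99.8% for a school-level test, and 100% rejection for a uniform shift) rest on assumed effects of half a standard deviation and no clustering.

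The type I error inflation is conditional on pupils being the blocks. Its direction is then clear for any positive school-by-period ICC. Its size is not known from the documents: 0.060 to 0.288 for pre/post and 0.077 to 0.570 for four occasions, over assumed ICCs of 0.01 to 0.20.

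This should be fixed before the exposure data are analysed. It does not threaten the primary health analysis.

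**What to change.** Remove the Friedman test and name the period-by-location interaction as the work package 2 personal-exposure contrast. Then specify one of the following:

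- **School-level analysis.** Compute one pre-to-post change score per school and compare the three location groups across 12 schools, by permutation test or by an F test on 2 and 9 df. The F test held its type I error at 0.040 to 0.055 at every ICC tried.
- **Linear mixed model.** Use fixed effects for period, location and their interaction; random effects for school, school-by-period and pupil; and small-sample degrees of freedom. The school-by-period term is essential, for the reason in step 6 of the working.

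State the unit of analysis in either case. The change is to the analysis wording and calls for no extra measurement. The price is visible precision: results will look less certain than in a pupil-level test, because the comparison rests on 12 schools.
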